##### Transcutaneous vagus nerve stimulation (tVNS)

The tVNS device (“Nemos®”; cerbomed GmbH, Erlangen, Germany) (Fig. 2) stimulates the afferent auricular branch of the vagus nerve located medial of the tragus at the entry of the acoustic meatus [70]. This device has received CE approval as indication that it complies with essential health and safety requirements [71]. The ear is first cleaned with an alcohol wipe and the electrode is sprayed with a conductive fluid to ensure optimal stimulation. Two titan electrodes mounted on a gel frame are connected to the Nemos® pocket-size stimulator and placed in the concha of the left ear in order to avoid stimulation of fibers to the heart. Stimulation intensity is individually adjusted (from 0.1 to 10 mA) with a pulse width of 250 μs and a consistent stimulation frequency of 25 Hz for optimal stimulation [72]. During CVI, participants will familiarize themselves with the stimulation device and its proper usage under the guidance of the testing administrator. During this visitation, the intensity of the tVNS will be slowly increased until the optimal intensity (mA) is reached (i.e., a slightly uncomfortable tingling sensation) for each individual participant [53]. Both active and sham stimulation constantly alternate between active stimulation for 30 s, followed by a break of 30 s [73]. Participants will perform active or sham tVNS at home for 15 min [61] in the morning upon waking and 15 min at night before going to bed (preferably at the same time for each individual participant) for a total duration of 2 weeks. Due to habitation, participants will be allowed to readjust this stimulation intensity during their 2-week intervention period if needed.
(A)*Active tVNS* is performed in a relaxed position, sitting back in a chair no more than 30° from the horizontal, with both feet flat on the floor, and hands on thighs with palms facing downward. The bipolar stimulation electrode is placed correctly within the concha of the left ear. Participants are instructed to breathe normally while not talking or making any movements during their session.(B)*Sham tVNS* is performed in a relaxed position, sitting back in a chair no more than 30° from the horizontal, with both feet flat on the floor, and hands on thighs with palms facing upward. The bipolar stimulation electrode is turned 180° and placed incorrectly over the center of the left earlobe instead of the outer auditory canal [15]. This area is known to be free of cutaneous vagal innervation [17] and produces no activation in the cortex and brain stem [15]. Participants are instructed to breathe normally while not talking or making any movements during their session.

**Fig. 2 Fig2:**
[figure not shown]
tVNS device. Nemos® transcutaneous vagus nerve stimulation (tVNS) device (Figure taken from [69])

### Data acquisition

Testing administrators input data directly into Viedoc on a Windows 7 HP EliteDesk 800 G2 SFF desktop computer located in the clinical visitation room at the Department of Pain Management and Research, Oslo University Hospital, Ullevål. Height is recorded with a Seca 206 (Seca GmbH, Hamburg, Germany) device which is bolted into the wall and leveled. Weight is obtained using an ADE M320000 (ADE Germany GmbH, Hamburg, Germany) digital electronic floor scale. Waist and hip circumferences are recorded with a MyoTape (AccuFitness, LLC, Greenwood Village, USA), and BP is taken utilizing a Philips IntelliVue MMS X2 (Philips Medizin Systeme GmbH, Hamburg, Germany) multi-measurement module and transport monitor.

**Fig. 3 Fig3:**
[figure not shown]
Signal processing pipeline for CameraHRV (Table taken from [80])

This study will use resting HRV recordings of 1 min. Reducing the HRV recording window to a duration of 1 min, in comparison to the standardized 5-min recording, is acceptable when rMSSD is considered as the primary HRV parameter of interest [81]. A 1-min recording of the natural log of rMSSD (lnRMSSD) has also been proven to offer good reliability in comparison to the classical 5-min recording of rMSSD [82]. Furthermore, high-frequency HRV (hfHRV) also shows reasonable agreement between ultrashort-term recording windows (60 s or less) and 5-min periods [82, 83]. Several studies use hfHRV as an index of vagal tone [47] due to its strong correlation with rMSSD [84, 85]. However, unlike hfHRV, rMSSD has been shown to be insusceptible to confounding respiratory effects during the recording window [26, 83]. In addition to the main analysis performed with one ideal variable reflecting vagal tone (RMSSD), it is recommended [47] that researchers perform the same analyses with the other variables depicting vagal tone (hfHRV, SDNN, and pNN50). Date and time of day for every HRV recording will be saved within the CameraHRV program which can be used as a proxy for treatment compliancy for all participants during their 2-week home treatment.

#### BarTek™ (Fig. 4)

The BarTek™ respiratory gating device (VRMind, Wroclaw, Poland) designed for practicing MNRB™ measures abdominal expansion via strap tension that is induced by the diaphragm during the entire respiratory cycle. The elastic strap of the BarTek™ sensor is placed around the waist of each participant and is adjusted in length in order to produce a minimal resistance to respiratory movement. Tension measurement is implemented by a strain gauge circuit. This circuit contains a strain gauge measurement element, and a temperature compensation element. High-precision measurement is ensured by using a high-resolution analog digital converter. Device output signal has an electric potential difference that is sampled at 80 Hz. The signal is transmitted to the Krüger&Matz Flow 5 Android smartphone via a Bluetooth Low Energy protocol. Date and time of day along with all respiratory information will be recorded and saved within the MNRB™ program. The raw signal processing used in order to obtain each participant’s respiration dynamics (e.g., rate and volume) is shown in Fig. 5.

**Fig. 4 Fig4:**
[figure not shown]
BarTek design

**Fig. 5 Fig5:**
[figure not shown]
Signal processing pipeline for BarTek device. Real-time signal processing is based on a zero-crossing algorithm with further modifications. It is important to note that zero-crossing detection is based on a dynamically adjusted threshold. The basic signal processing algorithm consists of seven steps

#### DoloCuff

Computerized cuff-pressure algometry (CPA) will be administered using the DoloCuff device with software version 2.0.5.1 (DoloCuff; Unique Electronic Aps, Hvidovre, Denmark) in order to assess clinical pain sensitivity mechanisms in FM patients. The DoloCuff CPA consists of a double-chambered 13-cm-wide textile high-pressure 13.5 cm × 76 cm tourniquet cuff (VBM Medizintechnik GmbH, Sulz, Germany), a computer-controlled air compressor (Unique Electronic Alps), a 10-cm electronic visual analog scale (VAS), and a stop button for immediate release of air in the tourniquet cuff. The tourniquet is tightly mounted around the widest part of the m. gastrocnemius in order ensure reliable pressure readings.

Ramp inflation of 1 kPa/s [86] will be used in order to record a participant’s pain detection threshold (PDT), pain tolerance threshold (PTT), pressure pain limit (PPL), and stop time [87]. Cuff PDT is defined as the pressure value the first time the VAS score exceeds 0 (i.e., at the moment of transition from a sensation of strong pressure to first sensation of pain) whereas cuff PTT is defined as the pressure value when the participant terminates the pressure inflation (i.e., when the pain due to the pressure of the cuff becomes intolerable) [87]. A maximum pressure of 150 kPa and a maximum time under pressure of 180 s are set as the upper limits throughout the study [88]. The maximum pain intensity (VAS peak) and time to VAS peak will be extracted along with the individual slopes in pain intensity rise and fall from the start of cuff inflation to the end of cuff inflation. Areas under the VAS curve are also calculated based on raw data [89].

#### ViedocMe

Participant-reported outcome measures (PROMs) in the form of questionnaires (see below) will be completed electronically using the ViedocMe functionality available in Viedoc at CVI and CVII. Study staff will create a ViedocMe account for each participant in the participant’s Clinic View in Viedoc and provide a unique log-in profile (username, pin code, and ViedocMe web address) for each participant. Participants are to use this information to log in to their personal ViedocMe account on a tablet (Samsung Galaxy Tab A6 32GB) which is connected to Oslo University Hospital’s secure wireless account. The questionnaires in ViedocMe will only be available for completion the day of each clinic visitation. Participants will complete the questionnaires at the end of each visitation. After the time-window has expired (i.e., at midnight on the day of the clinic visit), questionnaires can no longer be completed electronically. If problems arise using ViedocMe, or if the participant prefers to use paper forms, paper copies of the questionnaires will be handed out to the participant and the data will be entered into Viedoc by testing administrators. Questionnaires are only available to participants in Norwegian. For a list of names with descriptions of each questionnaire utilized in this study, see the Appendix.

List of questionnaires in the order of their completion:

Credibility Expectancy QuestionnaireParticipant Global Impression of ChangeEQ-5D-5LHopkins Symptom ChecklistMultidimensional Assessment of Interoceptive Awareness, version 2Spiritual and Religious Attitudes in Dealing with IllnessPain catastrophizing scaleBrief Pain InventoryInsomnia Sleep InventoryOswestry Low Back Pain Disability QuestionnaireGeneral Health Questionnaires

#### Daily treatment journal

Participants will receive a take-home Daily Treatment Journal where they will record their treatment session day, time (morning or evening), pre- and post-treatment HRV recording (Yes/ No), and pre- and post-treatment NRS pain intensity. Participants will also be instructed to write any thoughts, feelings, and/or reflections in regard to their overall treatment experience. Upon completion of the 2-week treatment, participants will hand their Daily Treatment Journal to the assigned research administrator at CVII where it will be recorded directly into Viedoc.

### Data collection procedure

#### Clinical visitations I and II (Fig. 6)

Testing administrators will conduct all data collection for CVI and CVII at the Department of Pain Management and Research under the supervision of the principal investigator. All data will be collected by the same assessor throughout each visitation. From 8:00 to 12:30, three participants will be consecutively registered upon arrival at the Department and directed to the clinical visitation room by an assigned testing administrator. Upon entering the visitation room, each participant will be given an informed consent and will be offered the time to ask any questions in regard to what is required of them for their participation. Upon signing the informed consent, measurements of height, weight, BMI, and WHR will be made. Participants will be instructed to remove any heavy clothing and footwear when on the digital electronic floor scale. BMI will be calculated as weight in kilograms divided by the square of the height in meters (kg/m^2^). After recording the aforementioned measurements, participants will sit in a relaxed semi-Fowler position (30° tilt from the horizontal) with feet flat on the floor, hands on thighs, and palms facing upward for the remainder of the clinical visitation. Any discrepancies to the procedure will be logged in Viedoc and kept for the remainder of the study period and will be included as a potential confounder in analyses.

**Fig. 6 Fig6:**
[figure not shown]
Clinical visitations. **a** Clinical visitation 1 (CVI). **b** Clinical visitation II (CVII)

The assigned testing administrator will then conduct a clinical interview at CVI in order to confirm a diagnosis of FM, including FM, and in CVII in order to determine how or if the pain has changed. Participants will be guided through an electronic version of the 2016 revision to the 2010/2011 FM diagnostic criteria form [44] digitalized in Viedoc by the lead author ([name]). Prior to the FM diagnostic confirmation interview, participants will be asked to numerically rate their pain in the following manner: “On a scale of 0 to 10, where 0 corresponds to no pain and 10 corresponds to the worst possible pain you can imagine; (1) How strong would you say that the pain usually is?; and (2) How strong is the pain now?” If participants are confirmed to have FM with an average (i.e., usual) pain intensity NRS ≥ 6, they are instructed to remain seated in a semi-Fowler position (no more than 30° from the horizontal), with eyes closed, and breathe normally without speaking or making any movements [47]. For CVII, there are no diagnostic criteria cutoffs for FM and average pain intensity.

The testing administrator will then conduct a visit compliance interview immediately following the FM diagnostic interview for each visitation. Participants are instructed prior to visitation to follow a normal sleep routine [90] and abstain from any type of intense physical training the day before each clinical visitation [91]. Participants are also asked to abstain from drinking coffee, any type of energizing drinks [92], and tea [93] 2 h before each clinical visitation. Furthermore, participants are instructed not to drink alcohol 24 h prior to their visitations [94] or eat within 2 h of their visitation [95] (eating/digestion [96], missing a meal [97], or smoking [34] can significantly influence HRV). If patients do partake in the aforementioned actions, this information will be accounted for at this time. Upon completion of the visit compliance interview, testing administrators will note the sex of each participant and any cardioactive medications that they are taking. The computer-generated randomized allocation sequencer in Viedoc then generate the randomization number as well as the allocated treatment group for each participant (e.g., tVNS #1 (active); tVNS #2 (sham); MNRB™ #1 (active); MNRB™ #2 (sham)).

In order to acclimatize to the HRV recording environment, each participant is instructed to remain seated for at least 5 min [98] prior to taking the first HRV measurement (Fig. 7a). Acclimatization helps reduce HRV changes due to posture changes [99, 100] and can also reduce confounds subsequent to participant test anxiety [26]. Immediately following the 5 min acclimatization period, three 1-min HRV recordings will be taken on the tip of the right index finger of each participant separated by 1-min intervals. The beginning and end of each of the three HRV recordings will not be announced due to the impact of attentive states and test anxiety on respiratory frequency [101] and HRV recordings [102]. An average of the last two recordings will be used as the baseline measure.

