### Randomization and blinding procedure

#### Randomization

The computer-generated randomized allocation sequencer will be imported into the Viedoc eCRF system and made available to testing administrators. Only testing administrators will have access to participant treatment allocation and the allocation will not be available until the participant has signed the informed consent and deemed eligible to participate in the study.

This investigation will use a list randomization recruitment method [50] for CVI where participants will be randomly allocated to receive one of the four treatment groups: tVNS #1 (active); tVNS #2 (sham); MNRB #1 (active); MNRB #2 (sham). The randomization will be stratified by sex (male = 1, female = 2) and cardioactive medications (yes = 1, no = 0) with varying block size within strata. Viedoc will generate the randomization number as well as the allocated treatment group for each participant.

Participants will be considered as taking cardioactive medication if they report that they are currently taking any medication for high BP, cholesterol, heart disease, or prescription pain medication. Participants will also be considered as taking cardioactive medication if they answer that they use tranquilizers, antidepressants, and/or antipsychotics either “less than every week,” “every week, but not daily,” or “daily.” Participants are permitted to continue taking any previously prescribed pain medications/psychopharmacological treatments that are necessary during the trial period.

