#### Blinding

The blinding strategy utilized in this clinical trial follows guidelines previously set forth and designed specifically for non-pharmaceutical intervention trials [51]. As recommended [52], research design elements such as treatment type, active and inactive treatment mechanisms, and research hypotheses are concealed from participants, testing administrators, and data collectors. Active and sham treatment allocation is concealed from the participants and testing administrators. Both testing administrators and study participants will be told that they will provide/receive two different *versions* of nerve stimulation at different locations on the ear (for the tVNS group) or that there are two breathing techniques that are being explored (for the MNRB group) in this investigation [53]. The testing administrators will introduce either “Version 1” (active) or “Version 2” (sham) of the treatment interventions.

The principal investigators ([name] and [name]) are blinded to patient treatment allocation as well as the randomization form in Viedoc. This form will only be visible to the testing administrators performing participant data collection. To protect against export of blinded data during the study, there will be two export roles in this study: (1) blinded export and (2) unblinded export. Blinded data export role will be given to the investigators prior to database lock while the unblinded data export role will be given to the investigators only after database lock.

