For clinical visitation I, each participant will be introduced to their assigned treatment (tVNS or MNRB™) and version (version 1 or 2). Testing administrators are to motivate each participant to complete the treatment and provide instructions on how to use the devices throughout the 2-week intervention period. In addition to a verbal introduction of each treatment version, testing administrators will also guide participants in a short 5-min trial period during which the treatment is properly setup and tested. This is helpful in demonstrating to participants the functionality and design of their treatment. Participants are welcome to ask any questions or share any concerns in regard to the procedure and what is demanded of them at this time. When the treatment introduction and trial period is complete for CVI, participants will receive their Daily Treatment Journal (or return it at CVII) and complete questionnaires in their ViedocMe account (For assessments as a function of timepoints according to the 2013 SPIRIT guidelines, see Table 2). Patients who receive one version of the treatment will be voluntarily offered the second version 6 months after the end of the study if they are still in pain and the results of the study justify this.

**Table 2 Tab2:** Assessments as a function of timepoints (according to the 2013 SPIRIT figure guidelines)

Measure	Target	T0	Intervention	T1
		*Baseline*	*Morning and evening treatment (4 recordings/day)*	*Post-intervention (2 weeks)*
NRS	Average pain intensity	X		X
NRS	Current pain intensity	X	X	X
HRV	Hear rate variability	X	X	X
BMI and WHR	Body mass index and waist-to-hip ratio	X		
BP	Blood pressure	X		X
CPA	Experimental pain threshold, tolerance, and limit	X		X
CEQ	Treatment efficacy expectation	X		
PGIC	Treatment efficacy impression			X
EQ-5D-5L	Health-related quality of life	X		X
HSCL-25	Stress and depression	X		X
MAIA-2	Interoceptive awareness	X		X
SpREUK-15	Spirituality	X		X
PCS	Catastrophizing	X		X
BPI	Pain interference	X		X
ISI	Insomnia	X		X
ODI	Functional disability	X		X
General health	Overall health/nutrition and sociodemographic	X		

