## Appendix

### Participant-reported outcome measures (PROMS)

#### Numeric rating scale

The numeric rating scale (NRS) [128] will be used to assess pain intensity. Participants are asked to circle a number between 0 and 10 that best describes their pain intensity—zero indicates “no pain at all” whereas the upper limit represents “the worst pain ever possible.” The NRS is a self-administered, public domain scale [128] that describes a less-subtle distinction of pain levels unlike the VAS/GRS, where there are an unlimited number of possible answers [129]. However, as in VAS/GRS, a change on the NRS of 20% between two timepoints of an assessment is considered clinically significant [57, 58]. Numerical rating scales correlate highly with other pain assessment tools [130, 131] and have good compliance [58] and reliability. In addition to clinical visitations I and II, participants are to complete the NRS pre and post MNRB/tVNS intervention every day (four times per day) and record their response in their Participant Journal.

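### The clinic pain NRS is described both as an interview question and as a self-completed scale, and masking of the person asking at CVII cannot be relied on, so average pain is open to interviewer influence

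*Protocol article*

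**What the plan says.** All references are to the protocol article.

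- **Mode at the visits.** Under Clinical visitations I and II, "The assigned testing administrator will then conduct a clinical interview at CVI", and again at CVII, where its purpose is to establish whether and how pain has altered. The usual-pain and current-pain questions are given as a script: "Prior to the FM diagnostic confirmation interview, participants will be asked to numerically rate their pain in the following manner". That the ratings are also taken at CVII follows from "For CVII, there are no diagnostic criteria cutoffs for FM and average pain intensity", from Table 2, and from the planned CVI-to-CVII change scores.
- **Mode in the Appendix.** "The NRS is a self-administered, public domain scale". The participant circles a number, and the same paragraph names both clinic visits as well as the home ratings.
- **Self-completion route.** The ViedocMe section lists the questionnaires completed on the tablet, with paper as the alternative. The NRS is not on that list.
- **Who collects.** "Testing administrators will conduct all data collection for CVI and CVII".
- **Who can see the allocation.** Under Randomization, "Only testing administrators will have access to participant treatment allocation". Under Blinding, on the randomization form, "This form will only be visible to the testing administrators performing participant data collection". The visit procedure labels each treatment's two versions as #1 (active) and #2 (sham). The Limitations section treats unblinded experimenters as a weakness of the study.
- **Text the other way.** The Blinding section also says that active or sham status is hidden from the administrators, who are told only of two versions. Table 1 lists the outcomes assessor among the masked parties.
- **The administrator's other role.** At CVI, "Testing administrators are to motivate each participant to complete the treatment", and administrators also train participants in the assigned version.

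**The concern.** Pain intensity is subjective, and a reply given to an interviewer can be shaped by how the question is put or by a wish to please. If the person asking knows or suspects the version, that influence can differ between active and sham.

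The timing makes this matter for the contrast. At CVI the ratings come before the allocation is generated, so knowledge of the arm cannot affect them. At CVII they follow two weeks of treatment. A differential influence at CVII therefore passes straight into the change score and is not cancelled by the baseline value.

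The two accounts of mode also leave the site without one instruction to follow, and a reader of the results could not tell how the ratings were obtained.

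**Working it through.** **1. Mode.** The visit procedure places two scripted questions within an administrator's interview. The Appendix describes the participant marking a number and includes the same visits. The ViedocMe list gives the NRS no self-completion route in clinic. Taken together, the visit text reads as an interview and the Appendix as self-completion.

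**2. Masking of the asker.**

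| Points to access or no masking | Points to masking |
|---|---|
| Randomization: only administrators can see the allocation | Blinding: active/sham hidden from administrators |
| Blinding: randomization form visible to data collectors | Table 1: outcomes assessor masked |
| Visit procedure: labels pair #1 with active and #2 with sham | |
| Limitations: experimenters not blinded | |

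The statements cannot all hold, so masking at CVII cannot be assumed.

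**3. Which ratings are exposed.** In Table 2, average pain is recorded at T0 and T1 only. Current pain is also recorded during the intervention, circled by the participant in the journal four times a day. Average pain thus has no self-recorded counterpart; present pain does.

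**4. Size (illustration only).** The article gives no figure for interviewer bias and no SD for the NRS.

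*False-positive rate.* As a check on the tool, a two-sample t-test at d = 0.9 and two-sided alpha 0.05 needs 20.4, so 21, per group for power 0.80, and gives power 0.91 at 28 per group. The article's 21, and 0.9 at 28, are reproduced.

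Now take no true effect and a differential bias of b SD between active and sham. The non-centrality is b × √(n/2). With n = 28, √14 = 3.742.

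| Assumed b | Non-centrality, n = 28 | Rejection rate, n = 28 | Rejection rate, n = 21 |
|---|---|---|---|
| 0 | 0 | 5% | 5% |
| 0.1 | 0.374 | 6.6% | 6.2% |
| 0.2 | 0.748 | 11.4% | 9.7% |
| 0.3 | 1.122 | 19.7% | 15.8% |

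*Share of the clinical threshold.* The article calls a 20% NRS change clinically significant but does not say 20% of what. Of the 0-10 scale, it is 0.20 × 10 = 2.0 points. Of a qualifying baseline of 6 to 10, it is 0.20 × 6 = 1.2 to 0.20 × 10 = 2.0 points. An assumed shift of 0.25 to 0.5 points is then between 0.25/2.0 = 12.5% and 0.5/1.2 = 42% of the threshold. This is a loose yardstick, because the threshold is a within-participant change and the bias is a between-arm difference.

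**5. Room left to change.** Trial status dates this version 27 April 2020, with recruitment from 5 June 2019 to 1 August 2020. That is 327 of 423 days elapsed (77%). If accrual were even (an assumption), about 112 × 96/423 = 25 participants, or 6 per group, would remain.

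**The case against.** **Spoken delivery is inferred.** A reader might take it as stated that the administrator reads the questions aloud. The text says only that participants are asked, and the Appendix uses the same verb for circling a number. Fig. 6, the visit flow, is not available here. This stands as a limit on wording. The script and the interview setting still make asking by the administrator the natural reading, and the Appendix does not match it.

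**The asker may be masked.** The concealment sentence and Table 1 say so. This stops anyone from asserting that the CVII interviewer is unmasked, but it does not establish masking against the four contrary places. Nor does the article say that the person asking at CVII is the one who trained the participant at CVI; it fixes one assessor within a visit only.

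**Pain NRS is not uniquely exposed.** This is correct. The cuff thresholds rest on participant ratings and a stop button with the administrator present, and the FM criteria form is also guided. The NRS is also one of about a dozen entries under the key secondary heading, although it comes first.

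**Different anchor wordings.** Table 1, the visit text and the Appendix word the upper anchor differently. A reader might infer that participants saw different scales. These are English descriptions, and the article says the questionnaires are given only in Norwegian, so the inference is not supported.

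**The remedy is partial and late.** This also stands. Expectation and the administrator's training and motivating role would remain, and changing everyone at once would give participants then between visits a mixed-mode change score.

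**Conclusion.** The point holds as a conflict over how the clinic NRS is collected, joined to masking statements that cannot all be true. Its consequence is that the active-sham contrast in average pain, a subjective secondary outcome measured only at CVI and CVII, is open to interviewer influence at CVII. Present pain is less dependent on the clinic rating because it is also self-recorded at home. The primary outcome, HRV, is not touched by this point.

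The size is unknown. The rise to roughly 6.6% to 20% in the false-positive rate assumes a differential bias of 0.1 to 0.3 SD, 28 per group and a simple two-group t-test. The 12.5% to 42% share assumes a shift of 0.25 to 0.5 points. Neither range shows that bias has occurred. The documents do not support a claim that the interviewer is certainly unmasked, that a 2-point threshold is the protocol's own figure, or that self-completion would remove the influence altogether. The change is worth making because the means already exist, but it is not a fatal flaw.

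**What to change.** 1. Amend the visit procedure so that, at both visits, participants enter average and present pain themselves on the ViedocMe tablet, or on paper, before the interview. The administrator neither reads out the items nor prompts. At CVI the stored average-pain value is then used for the eligibility check.
2. Add the two items to the ViedocMe list, align the Appendix entry, and reconcile the statements in Randomization, Blinding, Limitations and Table 1 on what administrators know.
3. Apply the change only to participants whose CVI falls after a recorded date, so that nobody has one mode at CVI and another at CVII. For those already enrolled, record which mode was used and who asked.
4. Report average-pain results by mode, or adjust for mode.

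**Cost.** Two items move to an existing system, and the account must open after consent at the start of CVI and at the start of CVII, because the questionnaires are now completed at the end of each visit. The main drawback is timing. If only about 6 per group remain, most ratings will already be in the old mode and a comparison by mode will be imprecise. The documentation in steps 2 and 3 is useful even then.
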